#### Pre-specified subgroup analysis

Pre-specified subgroup analyses will be performed for the primary outcome and its components, the bile-acid and itch outcomes, using the statistical test of interaction (or test for trend). Binary outcomes will be presented as risk ratios with confidence intervals on a forest plot. Pre-specified subgroups will be based on the criteria selected for minimisation: serum bile-acid concentration at baseline (10–39 μmol/L/ ≥ 40 μmol/L); gestational age (participants recruited before 34 weeks, 34 to 36 + 6 weeks, ≥ 37 weeks’ gestation); singletons and twins.

#### Sensitivity analyses

Sensitivity analyses will be conducted for the primary outcome, itch and bile-acid concentration between randomisation and delivery, excluding mothers or infants of mothers did not adhere to the intervention (< 90% medication adherence consistently self-reported).

#### Level of statistical significance

Ninety-five percent confidence intervals will be used for all primary and secondary outcome comparisons including subgroup analysis.

#### Missing data

Missing data as a result of women or infants being lost to follow-up are expected to be less than 5%. All complete data items collected will be used. Case note review will be conducted as usual on women who discontinue the intervention, and on women who withdraw if they indicated consent for outcome ascertainment.

### Economic analysis

Data on mother and infant inpatient care and mode of delivery will be costed using nationally published sources. The cost of UDCA (derived from *British National Formulary*, National Institute for Health and Care Excellence) will also be included for women randomised to receive the intervention. Descriptive statistics will be reported including mean cost per participant and 95% confidence intervals constructed using bootstrapping.

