### Study procedures

#### Recruitment, eligibility and consent

Members of the research team will provide a full verbal explanation and written description of the trial to women who meet the inclusion criteria (as above). The woman will be given sufficient time to consider the information, and to decide whether she will participate in the trial. Written informed consent will be sought from the woman and taken by an appropriately trained physician. Baseline data, including all demography, serum bile-acid concentrations and liver function tests, together with an itch visual analogue score (worst itch in the previous 24 h) completed by the woman will be entered on a web-based database by members of the research team at the time of study enrolment. On completion of these details, the database will issue a pack number to the local hospital pharmacy for dispensing.

Participants will be reviewed at routine care clinic visits until delivery. Serum bile acids and liver function tests will be monitored according to usual clinical practice. The woman will be asked for a value of the worst itch she felt during the previous 24 h. The Investigational Medicinal Product (IMP) dose will be altered at the discretion of the responsible clinician. If maximal doses of the IMP have been reached, consideration can be given to the addition of other therapy, e.g. rifampicin, in addition to the trial therapy, without breaking the allocation code. The remainder of antenatal care, in particular the timing and mode of delivery will be left to the discretion of the responsible clinician. A schedule of participant enrolment, interventions and assessments in the trial is shown in Fig. 1.

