**Fig. 1 Fig1:**
[figure not shown]
Schedule of participant enrolment, interventions and assessments in the trial. 1. All screening assessments are part of routine clinical practice. 2. Weekly visits are recommended but not mandatory; normal hospital clinical practice is acceptable. 3. No other trial-specific procedures are required before consent. 4. These blood tests are taken as per routine clinical practice and are not trial specific. 5. Investigational Medicinal Product (IMP) started after randomisation. IMP dose altered by the research team if indicated by symptoms and/or blood tests taken during normal clinical practice. 6. Cardiotocography only measured 1 week after randomisation or as per routine clinical practice. 7. All unexpected adverse events occurring during the trial that are observed by the research team or reported by the participant will be recorded in the electronic Case Report Form, whether or not attributed to the IMP. Unexpected serious adverse events will be expeditiously reported. 8. All prescribed medications deemed necessary by the investigator to provide adequate supportive care for ICP are permitted during the clinical trial. The medications must be recorded in the participant’s electronic Case Report Form; all other concomitant medication will only be recorded in the event that a serious adverse event is reported

A woman will be free to withdraw from the clinical trial at any time without the need to provide any reason or explanation; and that this decision will not impact on any aspect of her ongoing clinical care. Women who withdraw will be asked if they are willing for their outcomes to be collected by case note review. If there is sufficient time within the existing study time-line, additional participants will be recruited up to the number of women who discontinued the intervention or withdrew.

Outcomes will be recorded on the web-based database through case note review by trained researchers after discharge of the mother and baby.

The end of the trial will be defined as the date when the trial database is locked. An end-of-trial declaration will be made to the Medicines and Healthcare products Regulatory Agency and the approving Research Ethics Committee.

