#### Perinatal

Known neonatal death up to 28 daysNumber of nights in each category of care (intensive, high-dependency, special, transitional and normal)Need for supplementary oxygen prior to dischargeNumber of days when supplemental oxygen is requiredNeed for ventilation supportAbnormal cerebral ultrasound scanConfirmed sepsis (positive blood or cerebrospinal fluid cultures)Necrotising enterocolitis (Bell’s stages 2 and 3)Seizures (confirmed by electroencephalography or requiring anticonvulsant therapy)Encephalopathy (treated with hypothermia)Other indications and main diagnoses resulting in neonatal unit admission for at least 4 h

The following health resource use post enrolment will be captured for economic analysis:Maternal: total number of nights (antenatal, intrapartum and postnatal) together with level of care including adult Intensive Care Unit; mode of deliveryInfant: total number of nights for the infant in the neonatal unit, together with level of care (e.g. neonatal Intensive Care Unit)The cost of UDCA in the intervention group

All primary and secondary outcomes will be considered up to infant discharge home (from the hospital where delivered) or transfer to another hospital.

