### Randomisation

The allocation ratio of intervention (UDCA) to control (placebo) arms will be 1:1. Randomisation will be managed via a secure web-based randomisation facility. A minimisation algorithm will be used to ensure balance between the groups with respect to study centre (approximately 30 centres), gestational age at randomisation (< 34, 34 to < 37, ≥ 37 weeks’ gestation), single versus multi-fetal pregnancy, and highest serum bile-acid concentration prior to randomisation (< 40 μmol/L, ≥ 40 μmol/L).

The minimisation algorithm will be generated by MedSciNet, which will hold the allocation code. Research teams at sites will approach women to confirm eligibility and the intervention will be allocated using the web-based randomisation to provide an alpha numeric pack number which will correlate with a pack to be dispensed by that site’s pharmacy. The trial is triple-masked: trial participants, clinical care providers, outcome assessors and data analysts will all be masked to allocation.

Emergency code break will be available, but clinicians requesting unmasking must be satisfied that it is a genuine emergency and that knowledge of the treatment allocation (either UDCA or placebo) is needed to guide the appropriate clinical management of the participant. In some cases this may be achieved without unblinding, by stopping the allocated treatment and treating the participant with UDCA.

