### Analysis

The analysis and presentation of results will follow the most up-to-date recommendations of the Consolidated Standards of Reporting Trials (CONSORT) group. Full details of the Statistical Analysis Plan are given in Additional file 1: Text S1. Analyses will be completed in Stata® version 13.1 or later. Unmasked data will only be made available for analysis after full database lock (after all data outcomes have been completed) or on request by the Data Monitoring Committee. All analyses will follow the intention-to-treat principle, i.e. all randomised women (and infants) will be analysed according to the treatment that they were allocated to, irrespective of the treatment they received or whether they received any treatment at all.

Demographic and clinical data will be summarised with counts and percentages for categorical variables, means with standard deviations for normally distributed continuous variables, and medians with interquartile or simple ranges for other continuous variables. All comparative analyses will be performed adjusting for minimisation factors at randomisation [15]. Centre will be included as a random effect. Both unadjusted and adjusted effect estimates will be presented, but the primary inference will be based on the adjusted estimates.

Binary outcomes will be analysed using log binomial regression models. Results will be presented as adjusted risk ratios plus confidence intervals. If any model does not converge, a Poisson regression model with robust variance estimation will be used [16]. Continuous outcomes will be analysed using linear regression models and results will be presented as adjusted differences in means with confidence intervals. Continuous outcomes will not be categorised for statistical testing unless pre-specified as an outcome (and clinically relevant). Unadjusted median differences with confidence intervals will be presented for skewed continuous variables, and an adjusted analysis using quantile regression will be presented if possible. Analysis of outcomes that are measured repeatedly over time (severity of itch and biochemistry measures) will use repeated measures analysis techniques. Alternatively, if the data are highly skewed, geometric means of the post-randomisation observations will be reported [17] and the trial arms will be compared using a geometric mean ratio, adjusted for the baseline measures and minimisation factors.

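### UDCA is costed by allocated arm, so any open-label UDCA given to placebo women is left uncosted while its effect on their inpatient care is counted

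*Protocol article*

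**What the plan says.** The costing rule appears twice in the protocol article. The Economic analysis section states that UDCA cost "will also be included for women randomised to receive the intervention". The health-resource list that closes the Outcomes section (under Perinatal) names "The cost of UDCA in the intervention group". The remaining cost items are hospital care: "Data on mother and infant inpatient care and mode of delivery will be costed using nationally published sources".

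Three other places bear on who may receive UDCA or another cholestasis drug:

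- **Randomisation**, in the paragraph on emergency code break: clinical management may in some cases be achieved without unmasking, "by stopping the allocated treatment and treating the participant with UDCA".
- **Recruitment, eligibility and consent**: once the maximal dose of trial medication is reached, "consideration can be given to the addition of other therapy, e.g. rifampicin, in addition to the trial therapy, without breaking the allocation code".
- **Fig. 1, note 8**: "All prescribed medications deemed necessary by the investigator to provide adequate supportive care for ICP are permitted during the clinical trial". The note continues: "The medications must be recorded in the participant’s electronic Case Report Form".

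The Analysis section applies intention to treat to all analyses, with women kept in their allocated arm "irrespective of the treatment they received or whether they received any treatment at all".

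**The concern.** Two kinds of resource are attributed by different rules. Nights, level of care and mode of delivery are counted as they happened, in the arm to which the woman was allocated. UDCA cost is switched on or off by the allocation itself. An intention-to-treat cost comparison would charge each arm with everything its women used, including UDCA given to women allocated to placebo.

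Under the stated rule, a placebo woman switched to UDCA brings the placebo arm whatever change in inpatient care follows, with no drug cost attached. The bootstrap intervals cannot show this, because they resample costs that already contain the zero. At stake is the difference in mean cost per participant between the arms, and in particular the part of it that is due to UDCA.

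**Working it through.** The article gives no unit cost, crossover rate or cost difference, so there is no stated figure to reproduce. The check is algebraic, and every rate below is assumed.

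**Notation**

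- c = mean cost per woman of all UDCA used in the UDCA arm.
- x = mean UDCA cost per woman in the placebo arm, as a fraction of c. If a share q of placebo women receive open-label UDCA, each costing a fraction f of c, then x = q × f.
- d = cost per user of another cholestasis drug; sP and sU = shares using it in the placebo and UDCA arms.

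**Step 1: open-label UDCA in the placebo arm**

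Suppose first that the plan costs all UDCA used in the intervention arm.

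- Planned increment in UDCA cost = c - 0 = c.
- Increment by actual receipt = c - xc = c(1 - x).
- Absolute overstatement = c - c(1 - x) = xc.
- Relative overstatement = c / [c(1 - x)] - 1 = x/(1 - x).

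| x (assumed) | Absolute overstatement | x/(1 - x) |
|---|---|---|
| 0% | 0 | 0% |
| 2% | 0.02c | 0.02/0.98 = 2.0% |
| 5% | 0.05c | 0.05/0.95 = 5.3% |
| 10% | 0.10c | 0.10/0.90 = 11.1% |
| 20% | 0.20c | 0.20/0.80 = 25.0% |

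If switched women use UDCA for half as long (f = 0.5), x is half of q. For example, q = 10% gives x = 5%.

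**Step 2: dependence on how the rule is read**

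The article does not say whether open-label UDCA given to women in the intervention arm is costed. Switching happens without unmasking, so it can occur there too. If a share y of that arm's UDCA is open-label and left out, the planned increment is c(1 - y) against c(1 - x) by receipt. The error is then c(x - y): zero when y = x, and reversed when y > x. The results in Step 1 are the case y = 0.

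**Step 3: other cholestasis drugs**

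These are permitted and recorded in both arms, and neither costing passage names them. Leaving them out overstates the UDCA-minus-placebo difference by d(sP - sU), which can have either sign. With d = c:

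| sP, sU (assumed) | d(sP - sU) | Net with x = 2%, y = 0 |
|---|---|---|
| 10%, 5% | +0.05c | 0.02c + 0.05c = +0.07c |
| equal | 0 | +0.02c |
| 5%, 10% | -0.05c | 0.02c - 0.05c = -0.03c |

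The net error therefore has no fixed sign once add-on drugs are included.

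**The case against.** The strongest reply is that this is a minor feature of a descriptive analysis.

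- **Rarity.** The route to open-label UDCA is in the emergency code-break paragraph and applies only in some cases. The ordinary path after maximal dose is another drug added to trial therapy. Nothing in the article suggests that 10% or 20% of placebo-arm treatment would be open-label UDCA. This stands, and it is why the lower values are shown. It does not make x zero: Fig. 1, note 8 is worded broadly enough not to exclude UDCA, and the Discussion reports that some units prescribe it routinely.
- **Denominator.** The percentages refer to the UDCA drug-cost increment, whereas the reported quantity is mean cost per participant, which includes maternal and neonatal inpatient care up to intensive care. This stands.
- **Condensed article.** A full costing list may be in a document not shown, so the absence of add-on drugs is weak evidence of an error. This stands for those drugs taken alone. It does not answer the UDCA point, because the article does not leave UDCA costing open: it states a rule, twice.

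A reader might go further and infer that the whole cost comparison is biased against UDCA, on the ground that placebo women will need more add-on therapy. The article does not state that. It is plausible if UDCA relieves symptoms, but the add-on term can go either way. A reader might also infer a distorted cost-effectiveness result; the article describes only descriptive statistics, including mean cost per participant with bootstrap intervals, and states no cost-effectiveness ratio or decision rule.

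**Conclusion.** The point holds in a limited form. UDCA cost follows allocation while inpatient resources follow what happened, and the protocol itself provides a route by which a placebo woman can receive UDCA. If all intervention-arm UDCA is costed, the error in the UDCA drug-cost increment can only be an overstatement, of x/(1 - x): about 2%, 5%, 11% and 25% for assumed x of 2%, 5%, 10% and 20%, and nil if no placebo woman receives UDCA. If open-label UDCA in the intervention arm is also left out, the error shrinks and may reverse.

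The effect on total mean cost cannot be computed from the article and is probably small beside inpatient cost. The direction of the add-on drug omission is undetermined. The primary outcome and the other clinical comparisons are unaffected.

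**What to change.** Replace the allocation-based wording in both places (the resource-use list under Outcomes and the Economic analysis section) with costing by receipt: trial UDCA in the intervention arm, open-label UDCA in both arms, and recorded additional cholestasis therapy in both arms, taken from the medication and dose records in the electronic Case Report Form. State the rule before unmasked data are released, and report the proportion of each arm receiving open-label UDCA so that readers can judge its weight.

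The cost is a small extra costing step on data that Fig. 1, note 8 already requires. Precision will be limited by how fully dose and duration were recorded, so any imputation rule for missing duration should be given with the result. No change to treatment or to trial conduct is involved.

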### Assessment of safety and reporting

At each clinic visit, a member of the clinical or research team will ask the woman if she has had any adverse events, and will ensure that she has appropriate clinical monitoring as routinely performed in each maternity unit. Standard definitions of an adverse event, adverse reaction, serious adverse event, serious adverse reaction and suspected unexpected serious adverse reaction will be followed. The relationship of each adverse event to the IMP will be determined by a medically qualified individual according to the usual definitions of causality. The period for safety reporting will be from first dose of IMP until discharge of mother and discharge of infant. Expectedness will be determined according to the Summary of Product Characteristics for UDCA. Standard reporting guidelines will be followed.

The following expected adverse events and serious adverse events are considered to be expected in this population of pregnant women or a result of the routine care/treatment of a participant and as such do not need to be recorded:Worsening pruritusAdmission in active labourAdmission for cervical ripening or induction of labourAdmission for caesarean sectionAdmission for assessment for suspected fetal compromise, including poor growth, or reduced fetal movementsAdmission for monitoring for hypertension, antepartum haemorrhage, suspected preterm labour, pre-labour rupture of the membranes or other reasons for monitoringAdmission for psychiatric or social reasonsAdmission for unstable lie or external cephalic version.

The following fetal and neonatal outcomes are pre-specified outcomes and as such will be recorded on electronic Case Record Forms but not expeditiously reported:Neonatal unit admissionStillbirth and perinatal death (within 7 days)Preterm delivery (< 37 completed weeks’ gestation)Meconium staining of the amniotic fluid or placentaSmall for gestational ageSeizuresEncephalopathy (treated with hypothermia)Need for respiratory support – ventilation via an endotracheal tube (ETT) or nasal continuous positive airway pressure (CPAP)Sepsis requiring antibiotics with symptoms or confirmed blood or cerebrospinal fluid (CSF) culture

An unexpected serious adverse event is any event that meets the definition of a serious adverse event and is not detailed in the list above as expected, including:Maternal deathMaternal acute hepatic failure resulting in admission to an intensive care setting or requiring liver transplantAny unexpected fetal or perinatal death unrelated to ICP

### Quality control and assurance

Initiation of each participating centre will be performed by the chief investigator or their delegate once all appropriate approvals are in place and the IMP has been shipped to the site. During the trial, ongoing on-site and central monitoring will be conducted.

The site principal investigator (PI), research midwife and their delegates from each recruiting centre will be fully trained in protocol adherence and able to deal with site-specific issues. They will then be responsible for delivering this training to all relevant site staff prior to opening their centre for recruitment. The PI and research midwife will also promote the trial, and ensure that all appropriate site staff, are kept fully appraised of issues such as recruitment status, informed consent, data collection, follow-up and changing regulations, so that the necessary recruitment targets are reached within the timescale.

The trial coordinator will monitor recruitment against targets, and monitor data collection completeness and quality on a day-to-day basis.

Throughout the trial, there will be central monitoring, overseen by the Project Management Group, Data Monitoring Committee, Trial Steering Committee and Quality Assurance Team, ensuring good communication between National Perinatal Epidemiology Unit trial team and the site staff. Trial monitoring will be conducted in accordance with the monitoring plan developed from the trial-specific risk assessment. The monitor will visit sites where anomalies are identified through central monitoring. Sites that are identified as requiring additional support will be visited by a member of the trial team or the monitor as appropriate to the particular issues.

The Data Monitoring Committee will look regularly at protocol adherence by site and by trial arm, including randomisation processes and patterns of allocation.

#### Participant confidentiality, data handling and record keeping

Data will be entered by trained researchers at site onto a web-based database with pre-specified sense checks and boundary checks. Data will be downloaded and stored securely at the Clinical Trials Unit on a monthly basis as a minimum. Data will be reviewed by midwife coordinators and queries raised where clarification is needed. Source data will be verified by a data monitor in 5% of records by comparison of source data against electronic data entry. Data management procedures will be carried out in accordance with National Perinatal Epidemiology Unit Clinical Trials Unit’s Standard Operating Procedures and the principles outlined within MedSciNet Clinical Trial Framework User Manual.

All paper documents will be stored securely and kept in strict confidence in compliance with the Data Protection Act (1998) and all trial data will be stored in line with the Medicines for Human Use (Clinical Trials) Amended Regulations 2006. Due to the nature of pregnancy research, data will be kept for a period of no fewer than 25 years in order to follow up on health-related issues which may become relevant in the future. At all times the personal data will be held securely and will not be used for any other purpose.

The dataset will be available to appropriate academic parties on request from the chief investigator in accordance with the data-sharing policies of King’s College London and the National Perinatal Epidemiology Unit Clinical Trials Unit, with input from the Co-investigator Group where applicable.

